### Data sources

#### Survey for baseline attributes

In-depth life course history online surveys will be administered to all consenting clients at both centers who meet sample criteria at intake. Surveys will be completed electronically on secure servers using Qualtrics. Both treatment and control samples complete the life course history survey. Participants are compensated with a one-time $30 Visa gift card incentive. The survey instrument improves reliability and validity by utilizing published peer-reviewed scales known to be reliable measures. Moreover, original measures were developed, evaluated, and improved utilizing participant-based design that included people who use drugs, SUD clinicians, and persons in recovery from SUD as question writers, focus group participants, and survey testers. The survey asks about past drug and alcohol use patterns, mental and physical health, employment, housing, family arrangements, outstanding legal issues and includes the ACE (Adverse Childhood Experiences) scale, Kessler K6 scale, and peer-reviewed questions from instruments utilized in the Boston Reentry Study [14]. The ACE instrument, which is a widely accepted measure of childhood trauma predictive of adult adversity, is used to evaluate additional barriers related to recovery and increased propensity towards substance misuse [44]. The K6 Kessler scale is utilized to detect moderate mental distress. Survey data will be used to form retrospective life history reports. With these rich data we can better isolate correlations between background and recovery and understand who struggles most with substance use and legal issues and what their triggers are. We can also examine baseline equivalence between participants randomized to the treatment and control groups. Consent and survey documents are available upon request to the PI.

#### Court Innovations user data to measure engagement with ODR

Court Innovations is an ODR tech startup which originated at University of Michigan Law School and provides the justice system platforms utilized in this research, which operate directly with courts, without lawyers. Court Innovations has agreed to share user data with us from clients consenting to participate in our research. We will obtain Court Innovations data for our participants each year following enrollment for two years. These data will offer search statistics, so we know who searches for a case and when, if they officially make a request to begin a resolution with the court, and the disposition of the resolution with all communications between litigants and the courts. As discussed later, it will also help to determine [1] which participants randomized to the treatment group never utilized the software despite the hands-on training and [2] if any participants randomized to the control group utilized the software (e.g., through knowledge sharing between treatment group clients in clinics and their control group counterparts).

#### Treatment case files to measure treatment plan compliance

Primary outcomes are collected from electronic medical records. When consenting to participation, clients will be asked if they consent to us reviewing their treatment center electronic medical records during our intervention and two-year follow-up period. Treatment centers collect comparable metrics center to center because of local, state, and federal requirements and collaboration with Community Mental Health for Southeast Michigan, a primary funding and support resource for uninsured and Medicaid eligible persons diagnosed with SUD. Client demographics, contact information, substance use history, housing status, e.g., homeless, transitional housing, etc., mental health diagnoses, compliance with treatment, participation in 12-step programs, drug and sobriety court involvement, drug and alcohol histories and preferences, and when applicable, date of death will be examined.

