### Participants and clinical setting

The study inclusion criteria are (i) adult (aged 18 years or older), (ii) client receiving direct addiction recovery services at either partnering not-for-profit treatment center, (iii) Medicaid recipient or uninsured.

Participants may be male, female, or non-binary. Participants may be on probation or parole, but do not have to be. People who cannot read or lack computer literacy are eligible and will be offered direct support on these measures from research staff. Participants are offered the research instruments in English and may request a native Spanish speaking research team member and Spanish language research instruments during enrollment.

Two treatment centers are participating in our intervention and have multiple clinical and residential locations throughout Southeast Michigan, including over 180 transitional housing beds scattered throughout the county. Site locations include detoxification, inpatient, outpatient, and transitional housing. All clients are selected from a centralized case management system managed by a local public health agency that serves uninsured and Medicaid clients only. Length of treatment varies from 1 day up to about 2 years. Clients may be referred by friends, family, or law enforcement but also engage services on their own accord. One treatment center partner describes that their referrals often come from “courts, Friend of the Court [child support enforcement], Child Protective Services, Secretary of State, private attorneys, and other service agencies” [19]. Some clients are mandated to treatment in lieu of incarceration and may face incarceration if they fail to comply with the terms of treatment. Clients who participate in standard Drug Court or Sobriety Court typically are ordered to two years of intense supervision by a team of specialists which includes treatment components, but the specified treatment regimen, e.g., detoxification, residential, transitional housing, etc. varies by client.

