### Sample size justification

We intend to enroll 800 participants, with half of the clients randomly assigned to treatment (hands-on training with free ODR) and the other half randomly assigned to the control group (no ODR). A list of final study site locations may be requested from the primary investigator (PI). To determine whether we are sufficiently powered to detect an effect, we conducted a power analysis focused on the primary outcome: the client’s compliance with the treatment plan. We calculate the sample size needed for the study by applying the significance level of 0.05 and 80% power for a two-sided test. Since we lack both site-specific base rates of compliance and data on the possible effect size of hands-on training with ODR, we analyzed power along different dimensions of [1] base rates of treatment plan compliance in the control group and [2] possible improvements in compliance from the hands-on training with ODR. We set cases when the control group’s base rate of the treatment plan compliance ranges from 0.3 to 0.8 and then estimate the sample size necessary when the treatment group turns out to show 2–15% improvement from the control group. From this calculation, we find that 712 participants are necessary to find the difference between the compliance rate of 30% and 40% between the control and the treatment group. When the base rate of treatment plan compliance is 50% for the control group and 60% for the treatment group, we need 775 participants to find the distinction. If the compliance rate for the control group is 80%, 398 participants can inform us of the 10% difference between the two groups. Based on the result, we conclude that 800 participants allow us to detect a ~ 10% point improvement or larger; if compliance rates are high, we can detect much smaller improvements.

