### Study outcomes

The study outcomes in both groups will be measured at baseline (T0) and at one year (T1) and two years (T2) after baseline. The primary outcome will be substance use behaviors, which we use electronic medical records data to measure. Secondary outcomes measured with administrative data include (i) mortality, (ii) employment and earnings, (iii) justice system involvement, e.g., civil and criminal legal system encounters, (iv) housing status and household composition.^5^Table 1 shows the SPIRIT flow diagram for the schedule of enrollment, intervention and assessment.

**Table 1 Tab1:** SPIRIT diagram for the schedule of enrolment, interventions, and assessments

	Study period				
	Enrolment	Allocation	Post-allocation	Post-allocation year 1	Post-allocation year 2
Timepoint	- t1	0	T0	T1	T2
Eligibility	X				
Informed consent	X				
Allocation		X			
Interventions:					
Intervention group			X		
Control group			X		
Assessments:					
Primary Outcome			X	X	X
Secondary Outcome			X	X	X

The primary outcomes of interest are substance use behaviors. The secondary outcomes of interest are (i) mortality, (ii) employment and earnings, (iii) justice system involvement, e.g., civil and criminal legal system encounters, (iv) housing status and household composition (see Footnote 5)

The study outcomes will be measured at baseline (T0) and at year 1 (T1) and year 2 (T2) for both groups

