#### Potential additional data sources for secondary outcomes

In addition to the primary outcome, we will seek out administrative data on wages and employment status (Michigan Unemployment Insurance Agency), public benefit use, e.g., amount and duration (Michigan Department of Health and Human Services), and criminal justice interactions, e.g., charges, time served, community corrections, probation and parole interactions (State Court Administrative Office), so long as we continue the research. We will also apply to the National Center for Health Statistics (NCHS) National Death Index to collect mortality data for using the names, social security numbers, and/or birth dates of clients lost to follow up [45]. Clients will be asked to consent to administrative data linking. Records will not be linked without consent.

We will also supplement the administrative data with web scraping to collect additional data on mortality, also conducted with the consent of project participants. In particular, while the National Death Index (NDI) provides authoritative mortality statistics, there is a three-year lag where deaths in the year 2020 will not be searchable in the NDI until 2023, for instance. To provide more real-time measures of what has happened to clients that treatment centers have lost contact with, we will use web scraping focused on two types of data. First, is data that can help confirm a participant is alive but has potentially left Michigan. One easily accessible set of data is jail websites that post information on bookings [46]. We will conduct annual scrapes of the booking pages of jails in five neighboring states: Wisconsin, Illinois, Indiana, Ohio, and Pennsylvania. Second is data that can provide a more rapid estimate of mortality than the NDI: online notices of deaths in local newspapers, house of worship bulletins, legacy.com, and other sources. Other researchers have validated the use of online death notices against administrative records of deaths [47, 48]. Boak et al. [47], focused on Pittsburgh, found ~ 70% of deceased persons in the online notices. While the stigma of addiction related deaths may make online death data less reliable for this population, combined, the two sources can provide probabilistic estimates of what happens to participants whom treatment staff no longer are in contact with and who no longer appear in the Michigan administrative data sources.

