### Statistical methodology

We will summarize baseline and demographic characteristics using means and standard deviations (or interquartile ranges and medians) for continuous variables and percentages for categorical variables. We will report the proportion of eligible clients consenting to participate and other descriptive data on outcomes such as treatment compliance rates.

For identifying the causal impacts, our main analysis within the RCT will focus on two estimands. First, we will analyze outcomes among the intent-to-treat (ITT) sample, or those offered access to ODR regardless of whether they use the tool or have an eligible case. Because unobserved features of clients—for instance, their tech-savviness or how pressing their legal issue is—impact how clients use the tool, this provides the strongest causal estimate of the tool’s effect. Second, we will analyze outcomes among the “opt in and eligible sample”(TOT), which represents the effect of the assistance + tool on those who actually used the tools to resolve legal issues.^6^ This treatment-on-treated estimand is relevant for policymakers’ interpretations of the value of ODR for substance users—it corresponds to the counterfactual, “what would happen if we adjust the estimates to assume that we are able to tailor the offers to those who will actually use the tools and who have eligible cases to use them for?”

Our estimation approach will depend on the specific outcome variable in question and will be specified in greater detail in a later pre-analysis plan. Broadly, for the intent-to-treat “ITT,” we will examine using non-parametric differences in means (since covariates, in expectation, will be balanced across the groups due to the randomization) and linear and logistic regression, where the coefficient of interest is one on a binary variable for offer of treatment [49]. For the treatment-on- treated “TOT,” we will use the two-stage least squares approach where we regress our measure of compliance (“uses the ODR”) on the offer of the legal tool, and then use the fitted values from step one to measure the impact on outcomes. We will also use survival models for time-dependent outcomes (e.g., time to relapse; time to recidivism; time to mortality).

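### Substance use is named primary but comes from treatment-center records with no routine source after a client leaves care, so its ascertainment can differ by arm; make treatment completion or plan compliance the single primary outcome

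*Protocol article*

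**What the plan says.** Study outcomes states: "The primary outcome will be substance use behaviors, which we use electronic medical records data to measure". Measurement is at baseline (T0), one year (T1) and two years (T2). The data-source section on treatment case files adds "Primary outcomes are collected from electronic medical records" and identifies these as the treatment centers' own records, reviewed through the intervention and the two-year follow-up.

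Other sections bear on who is observed in those records:

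- Participants and clinical setting: "Length of treatment varies from 1 day up to about 2 years".
- Survey for baseline attributes: the survey asks about past use. No repeat is described.
- Potential additional data sources: wages, benefits, justice contacts and deaths. For "clients that treatment centers have lost contact with", the remedies are jail bookings, death notices and the National Death Index, which show whether a person is alive.
- Randomization procedure, Step 1: some clients return to a participating center more than once.
- Statistical methodology: "We will also use survival models for time-dependent outcomes (e.g., time to relapse; time to recidivism; time to mortality"). No source or observation window for relapse is given.

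Aims and objectives makes treatment completion the primary question. Sample size justification states: "we conducted a power analysis focused on the primary outcome: the client’s compliance with the treatment plan".

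**The concern.** Follow-up is two years for everyone, but many stays will be shorter. Once a client has left and does not return, no described source records use. That would be ordinary missing data if it fell equally on both arms for reasons unrelated to use. Here the intervention is meant to change whether clients complete treatment, so the time during which use can be recorded may itself depend on arm, and randomization does not protect against that. The article's own rationale also links exit to outcome: legal problems interrupt treatment when clients are jailed, and incarceration lowers the chance of recovery.

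At stake is whether the outcome named primary measures use, or use combined with length of contact. No later choice of estimator can recover use that was never recorded.

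**Working it through.** **1. The plan's own figures.** The design uses a "significance level of 0.05 and 80% power for a two-sided test" with 1:1 allocation. Per arm, n = [1.96·√(2p̄(1−p̄)) + 0.8416·√(p₁(1−p₁)+p₂(1−p₂))]² / (p₂−p₁)².

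| Compliance rates | n per arm | Total, arms rounded up | Stated total |
|---|---|---|---|
| 30% v 40% | 355.9 | 712 | 712 |
| 50% v 60% | 387.3 | 776 (774.7 before rounding each arm) | 775 |
| 80% v 90% | 199.0 | 398 | 398 |

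The figures reproduce. They concern plan compliance, not substance use.

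**2. Simple illustration.** Assumed inputs, none of them given in the article: 30% (control) and 40% (treatment) still in care at T1; true use 30% in care and 60% out of care in both arms.

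- True use: 0.3×0.3 + 0.7×0.6 = 51% v 0.4×0.3 + 0.6×0.6 = 48%, a benefit of 3 points.
- Among clients with records: 30% v 30%, no difference.
- No record counted as no use: 0.3×0.3 = 9% v 0.4×0.3 = 12%, an apparent harm of 3 points.

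In general the true difference is −(retention difference) × (use out of care − use in care). If use out of care were also 30%, the true difference would be 0, and restricting to clients with records would hide nothing.

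**3. A model over two years.** Assumed: 24-month relapse in control 70%, so the hazard is λ = −ln(0.3)/24 = 0.0502 per month; mean time in care m months, so the exit hazard is μ = 1/m. Relapse recorded while in care is λ/(λ+μ) × [1 − exp(−24(λ+μ))]. A share q of the remaining relapses enters the record through readmission. Clients without a recorded relapse count as relapse-free. Differences are from unrounded values.

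| Mean months in care, control / treatment | True HR | q | Recorded, control v treatment | Recorded difference | True difference |
|---|---|---|---|---|---|
| 6 / 6 | 0.8 | 0 | 23.0% v 19.3% | −3.7 | −8.2 |
| 6 / 9 | 0.8 | 0 | 23.0% v 25.8% | +2.8 | −8.2 |
| 6 / 9 | 0.8 | 0.25 | 34.8% v 34.8% | +0.1 | −8.2 |
| 6 / 9 | 0.8 | 0.5 | 46.5% v 43.8% | −2.7 | −8.2 |
| 6 / 9 | 0.8 | 1 | 70.0% v 61.8% | −8.2 | −8.2 |
| 6 / 9 | 1.0 | 0 | 23.0% v 30.5% | +7.4 | 0 |
| 6 / 4 | 1.0 | 0 | 23.0% v 16.7% | −6.3 | 0 |

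The last row has treatment clients leaving sooner: 0.0502/(0.0502+0.25) = 0.167, the final factor being close to 1. The bias then favors the intervention. With q = 0, a true hazard ratio of 0.8 is cancelled when treatment clients stay about 25–27% longer, and one of 0.7 when they stay about 43–47% longer.

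**4. Handling of leavers in a survival model.** Simulated hazard ratios, mean 3 months in care in control:

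| Handling | 33% longer care | 50% longer | 100% longer |
|---|---|---|---|
| True 0.8; no record = relapse-free | 1.05 | 1.17 | 1.47 |
| True 0.8; censored at exit, exit unrelated to risk | 0.80 | 0.80 | 0.79 |
| Full-data about 0.83; censored at exit, higher-risk clients leave earlier | 0.88 | 0.91 | 0.96 |
| True null; censored at exit, higher-risk clients leave earlier | 1.09 | 1.10 | 1.18 |

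**The case against.** The strongest reply has four parts.

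- **The records may reach beyond one stay.** Review covers the full two years, clients return, the settings include outpatient care and transitional housing, and the two centers are the main providers for this population. This stands. It is an inference that records exist only while a client is in care, and the article does not say so. Readmission reduces the bias, but in the table above it removes it only when essentially all later relapses come back into the record.
- **No handling rule is stated.** Nothing says that no record means no use, or that relapse is censored at last contact, and estimation is left to a later pre-analysis plan. This also stands. A reader might infer that a beneficial intervention will look harmful. The article does not support that: at a true hazard ratio of 0.8, reversal appeared only when no record counted as relapse-free. Censoring gave attenuation, or no bias if exit is unrelated to risk. The null row does show that informative exit can shift an estimate upward, so a benefit very close to nil is less protected.
- **More completion need not mean longer observation.** Completers are discharged too, and some stays are very short. This stands: neither which arm is observed longer nor the direction of the bias is fixed by the design.
- **Completion is already the primary question.** True of Aims and objectives and of the sample size, but Study outcomes and its table name substance use. The conflict makes the remedy inexpensive without removing the problem.

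Deferral to a later plan does not answer the core point, because the outcome, its source and its timepoints are fixed in this article.

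**Conclusion.** The concern holds in a limited form. As Study outcomes is written, the primary outcome depends on contact with the centers, and the intervention may change that contact. The effect on use can be attenuated if leavers are excluded or censored and leaving is related to use. For a benefit of the size examined, a reversed sign needs no record to be read as no use.

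The size is unknown: the article gives no retention, readmission or relapse rate, and every figure beyond the reproduced sample sizes rests on the assumptions shown. The problem does not extend to treatment completion or plan compliance, which can be determined for all randomized clients from the index episode.

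**What to change.** Reconcile Study outcomes and its table with Aims and objectives and Sample size justification. Name one primary outcome, index-episode treatment completion or plan compliance, with a single definition applied to every randomized client. Then:

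- Make record-based substance use and time to relapse secondary, labelled as use documented while in contact with the centers.
- State that no record is not counted as no use.
- Report observation time, including readmissions, by arm.
- For time to relapse, add an analysis in which unplanned exit without completion counts as an event, or as a competing event, instead of as independent censoring.

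**Cost.** Outcome wording and analysis text. Compliance with treatment is already among the fields to be extracted, and the sample size already rests on it. The article does not list a discharge-reason field, so the team should confirm that unplanned exit can be identified. In the added analysis some abstinent leavers count as failures, by the same rule in both arms. Use after planned completion stays unobserved under any of these choices, which is why a composite built on documented use would not be a sound replacement primary.

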#### Potential additional data sources for secondary outcomes

In addition to the primary outcome, we will seek out administrative data on wages and employment status (Michigan Unemployment Insurance Agency), public benefit use, e.g., amount and duration (Michigan Department of Health and Human Services), and criminal justice interactions, e.g., charges, time served, community corrections, probation and parole interactions (State Court Administrative Office), so long as we continue the research. We will also apply to the National Center for Health Statistics (NCHS) National Death Index to collect mortality data for using the names, social security numbers, and/or birth dates of clients lost to follow up [45]. Clients will be asked to consent to administrative data linking. Records will not be linked without consent.

We will also supplement the administrative data with web scraping to collect additional data on mortality, also conducted with the consent of project participants. In particular, while the National Death Index (NDI) provides authoritative mortality statistics, there is a three-year lag where deaths in the year 2020 will not be searchable in the NDI until 2023, for instance. To provide more real-time measures of what has happened to clients that treatment centers have lost contact with, we will use web scraping focused on two types of data. First, is data that can help confirm a participant is alive but has potentially left Michigan. One easily accessible set of data is jail websites that post information on bookings [46]. We will conduct annual scrapes of the booking pages of jails in five neighboring states: Wisconsin, Illinois, Indiana, Ohio, and Pennsylvania. Second is data that can provide a more rapid estimate of mortality than the NDI: online notices of deaths in local newspapers, house of worship bulletins, legacy.com, and other sources. Other researchers have validated the use of online death notices against administrative records of deaths [47, 48]. Boak et al. [47], focused on Pittsburgh, found ~ 70% of deceased persons in the online notices. While the stigma of addiction related deaths may make online death data less reliable for this population, combined, the two sources can provide probabilistic estimates of what happens to participants whom treatment staff no longer are in contact with and who no longer appear in the Michigan administrative data sources.

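### Death searching depends on loss of contact, a post-randomisation state that the intervention may change, so the mortality comparison can be biased in either direction and by different amounts in the two arms

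*Protocol article*

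**What the plan says.** Mortality is a secondary outcome (Study outcomes), and the Statistical methodology section plans a time-to-event analysis of it: "We will also use survival models for time-dependent outcomes (e.g., time to relapse; time to recidivism; time to mortality".

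Deaths and survival are to be ascertained from several sources:

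- **Treatment-center records** (Treatment case files). Clients are asked to consent to the team "reviewing their treatment center electronic medical records during our intervention and two-year follow-up period"; among the items, "and when applicable, date of death will be examined". This source is not restricted to lost clients.
- **NDI** (Potential additional data sources for secondary outcomes). The team will apply to "collect mortality data for using the names, social security numbers, and/or birth dates of clients lost to follow up". The section describes a three-year lag before deaths can be searched.
- **Web searches** (same section). These serve clients the centers have lost. One strand is "data that can help confirm a participant is alive but has potentially left Michigan", for which the text offers "One easily accessible set of data is jail websites that post information on bookings", covering five neighboring states. The other is online death notices, for which a cited study found about 70% of deceased persons. Combined, "the two sources can provide probabilistic estimates of what happens to participants whom treatment staff no longer are in contact with", provided these participants are also absent from the Michigan data.
- **Michigan wage, benefit and court data** (same section). These could show that a client is alive, but they are still being sought. Aims and objectives makes the secondary questions conditional on obtaining the linkages.

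No rule is given for the follow-up time or vital status of a lost client who matches nothing. Estimation detail is left to a later pre-analysis plan.

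**The concern.** Whether a client is lost is settled after randomisation. The primary question is whether the offer raises treatment completion, so if the intervention works as hoped, the arms may well differ in how long clients stay in contact. The trigger for an active death search would then differ by arm too.

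Two features add to this.

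- The sources that could show a lost client to be alive (employment, benefits, court contact, jail bookings) overlap with outcomes that the intervention is meant to change.
- The article does not say whether a client who completes treatment and leaves counts as lost. Treatment lasts from 1 day to about 2 years, so many clients may be out of center contact before year 2. If completers are not counted as lost, their later deaths have no stated NDI or web route. Nothing says the centers would learn of them.

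At stake is a comparison in which two arms with equal mortality appear to differ because of retention and data handling alone.

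**Working it through.** The article gives no mortality rate, loss rate or event count, so there is no figure of its own to reproduce. The check asks what apparent hazard ratio results when the true one is 1.

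**Inputs**

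- From the article: two-year follow-up; about 70% sensitivity of online notices.
- Assumed: annual mortality *m* = 2% or 5%; two-year loss of contact *L* = 30% in one arm and 50% in the other; exponential times; loss unrelated to death; complete NDI matching; deaths before loss all recorded by the centers.

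**Quantities**

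- Death hazard h = −ln(1 − m): 0.0202 at 2%, 0.0513 at 5%. Two-year survival S = exp(−2h): 0.9604 and 0.9025.
- Loss hazard g = −ln(1 − L)/2: 0.1783 at 30%, 0.3466 at 50%.
- Mean time between loss and year 2 for a client alive at year 2 (zero if never lost): E = 2 − L/g. This is 2 − 0.3/0.1783 = 0.318 years and 2 − 0.5/0.3466 = 0.557 years.

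**Rule 1: NDI searched for all lost clients, non-match read as alive to year 2.** All deaths and all person-time are kept. Estimated/true rate is 1.00 in both arms; hazard ratio 1.00.

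**Rule 2: deaths after loss counted, unmatched clients censored at last contact.** Deaths are complete, but living lost clients forfeit E years each unless a fraction f is confirmed alive:

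estimated/true rate = 1 / [1 − (1 − f) · k · E], with k = hS/(1 − S) = 0.490 at m = 2% and 0.475 at m = 5%.

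At m = 2%, f = 0:

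- 30% loss: 1/(1 − 0.490 × 0.318) = 1.18
- 50% loss: 1/(1 − 0.490 × 0.557) = 1.38
- apparent hazard ratio, higher-loss arm against lower: 1.376/1.184 = 1.16

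At m = 5% the ratios are 1.18 and 1.36, and the hazard ratio 1.15.

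**Rule 3: notices only, 70% of deaths after loss found, non-match read as alive.** The share of two-year deaths that follow loss is

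q = 1 − [h/(h + g)] · [1 − exp(−2(h + g))] / (1 − S),

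which at m = 2% is 0.158 (30% loss) and 0.277 (50% loss). Deaths found are 1 − 0.3q = 0.953 and 0.917 of the total. Missed deaths also add a little false person-time, bringing the rate ratios to 0.952 and 0.916. Hazard ratio 0.916/0.952 = 0.96. At m = 5% it is again 0.96.

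**Summary** (annual mortality 2%)

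| Handling of unmatched lost clients | Rate ratio, 30% loss | Rate ratio, 50% loss | Apparent HR |
|---|---|---|---|
| NDI, non-match = alive | 1.00 | 1.00 | 1.00 |
| NDI, censored at last contact, none confirmed alive | 1.18 | 1.38 | 1.16 |
| Same, 50% of living lost clients confirmed | 1.08 | 1.16 | 1.07 |
| Same, 80% confirmed | 1.03 | 1.06 | 1.02 |
| Notices at 70%, non-match = alive | 0.95 | 0.92 | 0.96 |

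A simulation with 2,000,000 clients per arm agrees with these values to within 0.01. The sign of the bias turns on the handling rule, and its size on how many living lost clients can be confirmed.

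**The case against.** A reader might infer more than this: that deaths are looked for only among lost clients, that lost clients who live are found only through jail bookings, and that mortality will therefore be overstated, most in the arm with more loss. The article does not support that reading.

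- Date of death is also taken from treatment-center records for any client.
- Living clients can reappear through Michigan wage, benefit or court data. Jail bookings are given as one example of a source, for people who may have left the state.
- Overstatement needs a specific rule, censoring unmatched clients at last contact while counting later deaths, and the article states no such rule. Reading non-match as alive removes the bias when the NDI is used and reverses it when only notices are used.
- The NDI is requested for the very clients whose records stop, so records and NDI together could cover everyone. Nothing says that notices or bookings will extend individual follow-up in the arm comparison.
- Estimation detail goes to a later pre-analysis plan, so the absence of a censoring rule is not a fault in itself.
- Mortality is secondary and its linkages are not assured.

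All of this stands against the stronger reading. It does not remove the narrower point. Whom to submit to the NDI is a data-acquisition rule that the article states. A later analysis plan can fix the censoring, but it cannot recover deaths among people who were never submitted. Complete coverage by records plus NDI also requires that everyone whose records stop is classed as lost, which the article does not say. The Michigan sources are uncertain for the same reason as the other linkages, and the intervention may influence who appears in them.

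**Conclusion.** The point holds in a limited form. Active death searching is tied to loss of contact, so the mortality comparison can be biased in either direction and by different amounts in the two arms. Under assumed loss of 30% against 50% and a true hazard ratio of 1, the apparent ratio ranges from 0.96 to about 1.16 according to how unmatched lost clients are treated. It is 1.00 where the NDI is used and a non-match counts as alive. If 80% of living lost clients are confirmed alive, the upward bias falls to about 1.02.

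These loss and mortality rates are illustrations, not figures from the article, and they take loss as unrelated to death. With equal loss in both arms the mechanism would still distort the mortality level, but under these assumptions not the comparison. The point is a worthwhile correction to a secondary outcome; it does not touch the primary analysis.

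**What to change.** In the section on additional data sources, change the NDI request to cover all consenting randomised participants, whatever their contact status. State for the mortality analysis that follow-up runs from randomisation to a common two-year cut-off for everyone, with participants unmatched in the NDI and not otherwise known to have died treated as alive at that date. Keep death notices and jail bookings for interim description only, and do not use them to extend an individual's follow-up in the comparison of arms.

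The costs are a modestly larger NDI request and a comparative mortality result that waits for the lag the article already describes. Consent to administrative linkage is already being sought from clients. Those who decline cannot be linked, and their number should be reported by arm.
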